## Abstract

**Background:**

The number of women of childbearing age with Type 2 diabetes(T2DM) is increasing, and they now account for > 50% of pregnancies in women with pre-existing diabetes. Diabetes pregnancies without adequate pre-pregnancy care have higher risk for poor outcomes (miscarriages, birth-defects, stillbirths) and are associated with increased complications (caesarean deliveries, macrosomic babies, neonatal intensive-care admissions). The risks and costs of these pregnancies can be reduced with pregnancy preparation (HbA1c, ≤ 6.5%, 5 mg folic acid and stopping potentially harmful medicines). However, 90% of women with T2DM, most of whom are based in primary care, are not adequately prepared for pregnancy. This study will evaluate a programme of primary care-based interventions (decision-support systems; pre-pregnancy care-pathways; pregnancy-awareness resources; professional training; and performance monitoring) to improve pregnancy preparation in women with T2DM.

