### Study design

A multimethod design will be used, with a clinical audit of PPC related processes and outcomes; and an integrated process evaluation informing intervention feasibility, implementation, and behaviour change; and an economic cost consequences analysis. The clinical audit will provide PPC performance data. Following CAS theory, we will use frequent repeat measures of the PPC performance metrics to monitor the delivery and impact of the intervention components at four-monthly intervals over 18 months from baseline (performance 12 months pre-intervention). At each timepoint performance measures will be reviewed to inform where intervention effects might need boosting or refining. The target performance for the intervention will be a minimum improvement of 30% at final observation in the proportion of women meeting current NICE pregnancy criteria [17]. Practice level performance will also be monitored considering the number of women: having a reproductive review; accessing PPC; receiving folic acid 5 mg; and instigated on contraception. Table 1 provides an overview of the data that will be used to determine systemic (across the exposed practices) and practice level performance (see Table 1). The PPC and pregnancy outcomes will have a relatively low incidence at the practice level so these will only be considered at the systemic level.

**Table 1 Tab1:** Performance measures

Performance measures	Systemic Performance	Practice Performance
Process data		
• Reproductive review and care plan instigated	Yes	Yes
• Care pathway activation	Yes	Yes
• Initiation of folic acid 5 mg	Yes	Yes
• Contraception advise given	Yes	Yes
• Instigated on contraception	Yes	Yes
• HbA1c testing and results	Yes	Yes
Pre-pregnancy care targets		
• HbA1c ≤ 48 mmol/mol (6.5%)	Yes	No
• Prescription of 5 mg folic acid pre-pregnancy	Yes	No
• Cessation of potentially teratogenic therapies	Yes	No
Pregnancy outcomes		
• Neonatal hypoglycaemia	Yes	No
• Macrosomia (birth weight > 4.5 kg)	Yes	No
• Shoulder dystocia	Yes	No
• Caesarean section incidence	Yes	No
• Neonatal intensive care admissions	Yes	No
• Postnatal length of stay	Yes	No
• Any other adverse outcomes	Yes	No

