### Data collection

The audit data (see Table 1) will be extracted from participating practices using an electronic template that we will install in the participating practices electronic record keeping system, the data collected will identify: women of child bearing age (< 45 years) attending appointments; reproductive assessments (activated on template); glycaemic control; changes to medications or contraception; PPC care-plan initiation; and PPC education or the dispensing of the integrated PREPARED self-help resources (leaflets and web-links). The pregnancy and pregnancy outcome data will be collected from the participating hospital audit systems which routinely collect these data for all women with diabetes as part of an ongoing national audit. The pregnancy booking data includes: glycaemic control; folic acid (5 mg) adherence; the prescription of any teratogenic therapies; and estimated pre-pregnancy weight. The birth outcome data includes: term and status of infant at birth including details of adverse outcomes; mode of birth; breast feeding status; maternal health/injury and depression; pregnancy complications; length of hospital stay; and neonatal care admissions. We will collect these data on all births during the observation period so we can compare outcomes in women from the intervention practices to unexposed practices. The hospital and practice level data will be extracted at baseline (12-month pre-PREPARED exposure) and then monthly to generate run charts monitoring process and outcome performance, with a full audit and review each quarter. The monthly data extractions will be continuous throughout the observation period (18 months). All data will be anonymised at source by hospital/practice administrators, practice codes will allow us to link them to the hospital data.

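### Hospital data for the exposed-versus-unexposed comparison are tied to births, so booked pregnancies that end before birth, including miscarriages, drop out if the sentence is followed literally

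*Protocol article*

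**What the plan says.** The Data collection section names the hospital source broadly: "The pregnancy and pregnancy outcome data will be collected from the participating hospital audit systems which routinely collect these data for all women with diabetes". It then gives two lists. The first is recorded at booking, before the end of the pregnancy is known: "The pregnancy booking data includes: glycaemic control; folic acid (5 mg) adherence; the prescription of any teratogenic therapies; and estimated pre-pregnancy weight". The second begins: "The birth outcome data includes: term and status of infant at birth including details of adverse outcomes; mode of birth". Directly after both lists comes the rule for the comparison: "We will collect these data on all births during the observation period so we can compare outcomes in women from the intervention practices"; the sentence goes on to name unexposed practices as the comparator.

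Other sections bear on the denominator and the outcomes:

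- The Abstract says that diabetes pregnancies without adequate preparation carry "higher risk for poor outcomes (miscarriages, birth-defects, stillbirths" and closes with the aim of reducing adverse pregnancy outcomes.
- Study setting, sample size and participants plans in pregnancies: 120–150 in the boroughs, of which 40–50 in exposed practices.
- Data integration and analysis says that antenatal as well as pregnancy outcome data will be compared between intervention and non-participating practices.
- Table 1 in Study design has no row for miscarriage. It has an open row, "Any other adverse outcomes", under pregnancy outcomes. The analysis section puts its own open category among the birth outcomes.

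**The concern.** The births sentence is an inclusion rule, and it states its purpose. Its reference to the data follows both the booking list and the birth list. On the plain reading, a woman who books and then miscarries contributes neither an outcome nor a booking record to the comparison.

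Two things are at stake:

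- A reduction in miscarriage, one of the harms that motivate the programme, could not appear in a births-only comparison.
- Folic acid use, glycaemic control and teratogenic prescribing at booking would be summarised only for pregnancies that reached birth. If unprepared women lose more pregnancies, the women who remain are better prepared than all women who booked, and the preparation measures in this comparison read too high.

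**Working it through.** **1. The plan's own counts.** The two hospital services care for 80–100 women with T2DM per year, and observation lasts 18 months.

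- 80 × 1.5 = 120 and 100 × 1.5 = 150, which reproduces the stated 120–150 pregnancies.
- 40/120 = 50/150 = 1/3, so the exposed share is one third at both ends of the range.

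These figures count pregnancies in hospital care, whereas the comparison sentence counts births. The article gives no rate that links the two.

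**2. The two readings of the births sentence.**

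- *Wide reading:* it governs both lists. Booked pregnancies that end before birth are lost with their booking data.
- *Narrow reading:* it governs only the birth outcome list. Booking data are kept for every recorded pregnancy, but miscarriage still has no named item, because the named birth outcomes concern delivery, the infant, and complications or care around them.

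On either reading miscarriage has no defined place in the comparison. On the wide reading the denominator for preparation is also wrong.

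**3. How many pregnancies could be affected.** Assumption, not in the article: 5–25% of recorded pregnancies end before birth. Births = pregnancies × (1 − loss).

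| Assumed loss | Births from 40–50 exposed pregnancies | Births from 120–150 borough pregnancies |
|---|---|---|
| 5% | 38–47.5 | 114–142.5 |
| 25% | 30–37.5 | 90–112.5 |

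The exposed group loses from 0.05 × 40 = 2 to 0.25 × 50 = 12.5 pregnancies.

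**4. What selection on birth could do to a preparation rate.** Let p be the prepared share among recorded pregnancies, a the loss in prepared women and b the loss in unprepared women. The share among births is p(1 − a) / [p(1 − a) + (1 − p)(1 − b)]. I take p = 10%, the current figure in the Background section, and p = 30%, the target level, used here only as a convenient value. The loss rates are assumed.

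| a, b | p = 10% | p = 30% |
|---|---|---|
| 10%, 10% | 10% | 30% |
| 10%, 20% | 0.09/0.81 = 11.1% | 0.27/0.83 = 32.5% |
| 5%, 25% | 0.095/0.77 = 12.3% | 0.285/0.81 = 35.2% |

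Overall losses in the last two rows are 17–23%, inside the assumed 5–25%. With equal losses there is no distortion.

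**5. Does it cancel between groups?** Only partly. Suppose the true rates were 30% in exposed and 10% in unexposed practices, a difference of 20 points. Among births the difference reads 32.5 − 11.1 = 21.4 points in the second row, and 22.8 points in the third (from unrounded shares).

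For scale, take 40 exposed and 120 − 40 = 80 unexposed pregnancies. Ignoring clustering by practice, the standard error of the difference is √(0.3×0.7/40 + 0.1×0.9/80) = 8.0 points. With 50 and 150 − 50 = 100 it is √(0.3×0.7/50 + 0.1×0.9/100) = 7.1 points. Under these assumptions the distortion of 1.4–2.8 points is well below sampling error.

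**The case against.** The strongest reply is that exclusion is inferred from one phrase. The births sentence comes right after the birth outcome list, and its evident purpose is to cover unexposed as well as exposed practices. The source sentence takes pregnancy data on all women with diabetes, and the analysis section speaks of comparing antenatal data. No section says that a booking record is discarded when there is no birth. This stands in part: the article is inconsistent, and a deliberate exclusion is not shown. But the births sentence is the only one that states for which pregnancies the comparison data are collected, and an extraction team could follow it as written.

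It can also be said that the open row in Table 1 could hold miscarriage. It could, but only if pregnancies that end before birth are in the data.

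The published article condenses a fuller protocol that may define the outcomes further. That would excuse an omission. It does not excuse a stated rule that conflicts with its neighbours.

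A reader might infer more than the text supports:

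- *That stillbirths and birth defects are lost too.* The birth data cover the status of the infant at birth with details of adverse outcomes, so stillbirth and anomalies seen at birth can already be collected.
- *That termination is one of the harms the programme aims to reduce.* The article never mentions termination. It matters here only because such a pregnancy would also leave the denominator.
- *That the 30% target is inflated.* The target is set among women from exposed practices, and the pooled practice-level data give the primary estimate. No section calculates it on births.
- *That fewer losses would make exposed practices look worse at birth.* Nothing in the article supports or quantifies this.

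**Conclusion.** The point holds as a badly fixed population for a secondary comparison. Followed literally, the births wording removes booked pregnancies that end before birth, so miscarriage cannot be counted between exposed and unexposed practices. It also conditions booking-based preparation measures on an outcome that preparation may affect. It conflicts with the broader pregnancy and antenatal data described in the same article and with planning figures that count pregnancies.

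The size cannot be computed from the article. The ranges above rest wholly on assumed loss rates, and the direction of any bias in preparation rates rests on the further assumption that unprepared women lose more pregnancies. If so, the distortion is likely to be modest beside the sampling error of 40–50 exposed pregnancies. The firmer consequence is that a named harm goes uncounted. The documents do not support reading this as a demonstrated bias in the study's main result.

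**What to change.** In Data collection, replace the restriction to births with: all T2DM pregnancies recorded by the two hospital services during the observation period, whatever their end. Then:

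- keep the booking data for every such pregnancy, and use recorded pregnancies as the denominator for preparation measures in the exposed-versus-unexposed comparison;
- report pregnancy loss after hospital contact, including miscarriage, as an outcome on that denominator;
- keep delivery measures such as caesarean section and shoulder dystocia on births.

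The cost is a slightly wider extraction from audit systems that the article already describes as covering all women with diabetes; the booking items are already listed. Pregnancies still under way when observation closes will have booking data but no outcome, and their number should be reported. Losses before hospital contact remain unseen, and the report should say so.

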Many of the risks associated with diabetes pregnancies can be ameliorated with improved pregnancy preparation and specific pre-pregnancy care clinic attendance. It is well established that exposure to hyperglycaemia and some treatments prescribed in the management of T2DM can harm the fetus during the period of organogenesis in the first trimester [13, 14]. Unfortunately, many women with T2DM are unaware of these risks [15] and may not realise they have conceived until late into the first trimester of their pregnancy [16]. In response, the National Institute for Health and Care Excellence (NICE) has developed guidelines for pre-pregnancy care (PPC) in women with diabetes which recommends: initiating high-dose (5 mg) folic acid; avoiding teratogenic medications; and intensifying glucose control [17]. However, the uptake of PPC is very low in the UK, with only 10% of women with T2DM meeting the current NICE criteria [3] increasing the risk of adverse pregnancy outcomes [18, 19]. It is also concerning that the majority of these women are from deprived areas and are from Black or Asian minority populations, thereby heightening underlying health inequalities [3]. Hence, establishing effective interventions to improve the uptake of PPC in women with T2DM is a high priority.

Previous prospective cohort studies investigating interventions to improve PPC uptake in women with diabetes have had a limited impact among women with T2DM, increasing uptake by only 7–15% [20–23]. These interventions have included: health professional education; patient information and education on PPC; PPC teams; and clinical guidelines [20–23].

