### Study setting, sample size and participants

The study will take place in South London where currently a high proportion of women with T2DM become pregnant without effective PPC [3]. We will recruit 30 general practices for intervention exposure. Practices will be considered for inclusion if they have ≥ 25 women with T2DM of reproductive age (18–45 years), this will provide a pooled sample of 750 women. Two local hospital diabetes pregnancy services responsible for the maternity care of 80–100 women with T2DM per year from this area will also participate, so that pregnancy outcomes can be studied.

It is difficult to predict how many women will be actively trying to conceive during the study period (this will be an important finding in itself), but we have estimated based on the number of annual pregnancies reported there will be 120–150 pregnancies in the participating boroughs: with 40–50 pregnancies in the women attending the PREPARED exposed practices. If we assume that women will be trying for pregnancies for 12 months prior to conception, then we can further estimate that > 100 women will be requiring PPC intervention with the remaining women (*n* =  > 650) requiring reproductive review and contraception.

There are high levels of deprivation and ethnic diversity in the local area, hence, establishing intervention reach into these communities is an important objective for the study as these groups of women form a major proportion of the target population.

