We will also report pregnancy interventions (initiation of additional hypoglycaemic agents) and birth outcomes (macrosomia, shoulder dystocia, caesarean rates, neonatal admissions, postnatal length of stay and other adverse outcomes); comparing practices exposed and not exposed to the PREPARED interventions. The process evaluation data will provide insights into cultural, interactional, and behavioural changes in relation to women and health professionals. These data will help us consider whether the intervention has changed the way care is delivered and how it is experienced by women with T2DM.

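### Comparing all births in the 18-month observation period would mix in roughly 42–50% conceived before PREPARED could act, diluting the secondary birth-outcome comparison

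*Protocol article*

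**What the plan says.** The Data collection section of the protocol article gives both the selection rule and its purpose: "We will collect these data on all births during the observation period so we can compare outcomes in women from the intervention practices" with outcomes in unexposed practices. The same section sets the timing: "The hospital and practice level data will be extracted at baseline (12-month pre-PREPARED exposure) and then monthly", with extraction running through an 18-month observation period.

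Data integration and analysis repeats the contrast. Birth outcomes such as macrosomia, shoulder dystocia, caesarean rate and neonatal admission will be reported, "comparing practices exposed and not exposed to the PREPARED interventions". The groups are defined by practice only. The article states no rule on conception date, no lag after go-live and no birth follow-up beyond month 18.

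On mechanism, the Background says that hyperglycaemia and some diabetes treatments "can harm the fetus during the period of organogenesis in the first trimester". The three pre-pregnancy care targets in Table 1 (HbA1c, 5 mg folic acid, stopping potentially teratogenic therapies) follow from this.

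**The concern.** The intervention is meant to work before conception, but births enter the comparison by their own date. A woman already pregnant when her practice goes live cannot receive PREPARED pre-pregnancy care. If her birth falls in the window, the article as written puts it in the intervention-practice group. For roughly the first 8 months, almost every birth in that group is of this kind.

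The resulting bias has a known direction: towards no difference. Estimating impact on pregnancy outcomes is a stated aim, and the analysis section promises a robust estimate of effects and costs. A real benefit could be reported as small or absent because the wrong pregnancies were counted. The cost comparison between exposed and unexposed women in Health economics would inherit the problem if it uses the same classification.

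**Working it through.** **Reproducing the article's figure.** The two hospitals are "responsible for the maternity care of 80–100 women with T2DM per year from this area". Over 18 months that gives 80 × 18/12 = 120 and 100 × 18/12 = 150, the article's 120–150 pregnancies. Its 40–50 in exposed practices is one third of this (40/120 = 50/150 = 1/3); that share is implied, not stated.

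**Inputs**
- Window W = 18 months (Data collection), read as starting at go-live because it follows a 12-month pre-exposure baseline.
- Conception-to-birth time g is not in the article. I assume delivery at 35–40 weeks from the last menstrual period, with conception two weeks after it: 33 × 7/30.44 = 7.6 months to 38 × 7/30.44 = 8.7 months. I take 9 months as the upper end.
- Births evenly spread, and all practices live at month 0.

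**Share conceived before go-live** = g/W
- 7.6/18 = 42%
- 8.3/18 = 46% (38 weeks)
- 9/18 = 50%

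If all 40–50 pregnancies ended in a birth (an upper limit), 40 × 0.42 = 17 to 50 × 0.50 = 25 births would predate any possible pre-pregnancy exposure. Between 40 × 0.50 = 20 and 50 × 0.58 = 29 would not.

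**Dilution.** Let r be the fraction of the full effect gained by pregnancies already under way. Observed effect / true effect = 1 − (g/W)(1 − r).
- r = 0: 0.50 to 0.58.
- r = 0.25 (illustration), g/W = 0.46: 1 − 0.46 × 0.75 = 0.66.

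**What this could do to one result (illustration only).** Take the Background caesarean rate of 50%, an assumed true halving, 50 exposed v 100 unexposed births, a two-sided 5% test and no allowance for clustering by practice.

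| Comparison | Difference | Power |
|---|---|---|
| All births exposable | 25 points | 85% |
| 46% conceived before go-live, r = 0 | 13.5 points | 34% |
| Restricted to later conceptions, 26 v 52 | 25 points | 56.5% |

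For neonatal admission (15%, same assumptions) the three powers are 24%, 9% and 13%.

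**Booking measures.** With booking at 8–12 weeks (assumed), the share conceived before go-live is (6 to 10 weeks)/18 months = 1.4/18 to 2.3/18 = 8–13%.

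**Cut-off at month 18.** A conception-date filter alone creates a second bias. A pregnancy conceived at month 10 is seen only if it ends within 8 months: 8 × 30.44/7 + 2 = 36.8 weeks. Late conceptions would therefore enter only when preterm.

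**The case against.** The strongest reply is that the quoted sentence is about data collection. A condensed article may leave the definition of the analysis set to a full protocol or analysis plan that is not shown, and collecting all births does not prevent a later restriction. That last part is true, and it is why the repair is easy. But the sentence names the comparison as its purpose, and the analysis section adds no condition beyond practice. The rule as stated should be corrected.

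Other parts of the defence stand:
- The comparison is secondary. The article introduces it as something it will also be able to do, with no test or decision rule. The target concerns pre-pregnancy care criteria.
- Monthly run charts against baseline could make the lag visible. They do not repair the pooled contrast between practice groups, and their early birth-outcome points cannot show a pre-conception effect.
- Even undiluted, the comparison is small: 24% power for a halving of neonatal admission.
- Timing is not fully settled. Study design speaks of measurement "at four-monthly intervals over 18 months from baseline (performance 12 months pre-intervention", and the flowchart is not shown. If the 18 months included the 12-month baseline, only 6 months would follow go-live and essentially all births would predate exposure. The Data collection wording makes that reading less likely.

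A reader might also infer that no birth can be properly exposed, because 12 months of trying plus 8 of pregnancy exceeds 18. The article does not support this. "If we assume that women will be trying for pregnancies for 12 months prior to conception" introduces a planning assumption used to count women needing care, not a required length of exposure, and women already trying at go-live can be reached.

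**Conclusion.** The concern holds for the birth-outcome comparison. With month 0 at go-live, evenly spread births and 7.6–9 months from conception to birth, about 42–50% of births in the window were conceived before PREPARED could provide pre-pregnancy care. Counting them as exposed pulls any pre-conception effect towards zero, to about 50–58% of its size if ongoing pregnancies gain nothing. The loss is smaller if the care pathway's links to maternity services help them. Staggered practice start-up would raise the share.

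It would go too far to say that the effect is certainly halved, that 40–50 births are affected (the article counts pregnancies, not all of which end in a birth), or that the main evaluation is undermined. The 30% target and practice process measures are not materially affected, and booking measures only slightly. This should be corrected before the birth data are compared; it is not a reason to hold up the study.

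**What to change.** 1. Define the exposed set for birth outcomes as pregnancies with an estimated conception date on or after the practice's go-live date. Derive that date from the birth date and recorded term (gestational age less two weeks), or use the last menstrual period throughout.
2. Apply the same calendar rule to unexposed practices, with the reference date fixed in advance if go-live is staggered.
3. Report earlier conceptions separately as pre-exposure.
4. Deal with the month-18 cut-off in one of two ways. Either limit the comparison to conceptions early enough to reach term by month 18 (about months 0–9) and say so, or, if feasible, take one further extract from the routine hospital audit about 9 months later.

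**Cost.** The first three steps need wording, go-live dates and gestational age. Term at birth is already on the data list; if it is held only as a category, weeks would have to be requested. Because records are anonymised at source, the hospital may need to derive the conception month. The main price is size: months 0–9 supply 9/18, about half, of the births otherwise expected (at most 20–25 of 40–50 in exposed practices). The later extract would recover all 18 months of conceptions but delays the birth-outcome report by about 9 months.

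### Birth outcomes are selected by birth date, so about 45–49% of in-window term births were conceived before launch and the exposed–unexposed birth comparison is diluted

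*Protocol article*

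**What the plan says.** Under Data collection, the protocol article fixes both the births to be used and their purpose: "We will collect these data on all births during the observation period so we can compare outcomes in women from the intervention practices" with those from unexposed practices. The window follows a 12-month pre-exposure baseline and lasts 18 months: "The monthly data extractions will be continuous throughout the observation period (18 months"). The Data integration and analysis section then plans to compare birth outcomes between practices exposed and not exposed to the programme. Exposure is therefore assigned by practice and eligibility by birth date. The article gives no conception-date restriction, no lag, and no birth follow-up after month 18.

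Two other statements show when the programme has to act. The Background says that hyperglycaemia and some diabetes treatments "can harm the fetus during the period of organogenesis in the first trimester". The sample size section sizes the need for pre-pregnancy care on a year of trying: "If we assume that women will be trying for pregnancies for 12 months prior to conception".

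**The concern.** A woman from an exposed practice who gives birth at term in month 4 was well into her pregnancy at launch. She could not have had a reproductive review, high-dose folic acid or a medication change through the programme before conceiving, yet she counts as exposed. Such births carry little or none of the pre-conception effect and pull the exposed–unexposed difference towards zero.

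At the other end, a woman who conceives late in the window has no term birth inside it. Changes made to the programme late in the study therefore cannot act before conception in any observed term birth.

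The Study objectives include estimating impact on pregnancy outcomes. If the birth comparison shows little or nothing, a reader could not tell a programme without effect from one that reached only part of the births counted. A positive result could also be credited to the final optimised programme, which these births did not receive before conception.

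**Working it through.** **The plan's own figure.** The sample size section gives 80–100 pregnancies a year at the two hospitals and 120–150 in the boroughs. 80 × 18/12 = 120 and 100 × 18/12 = 150, so the figure reproduces as an 18-month count.

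**Inputs.** From the article: an 18-month window, taken to open at launch. Assumed, because the article does not give them: conceptions spread evenly over time, term birth at 37–40 weeks from the last period (35–38 weeks from conception), first trimester ending at 13 weeks (11 weeks after conception), and 30.44 days per month.

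1. *Conception to term birth.* 35 × 7/30.44 = 8.05 months; 38 × 7/30.44 = 8.74 months.
2. *Share of in-window term births conceived before launch.* 8.05/18 = 44.7%; 8.74/18 = 48.5%. The rest, 55.3% to 51.5%, were conceived after launch. At 42 weeks the pre-launch share is 51.1%.
3. *Share already past the first trimester at launch.* 11 × 7/30.44 = 2.53 months. (8.05 − 2.53)/18 = 30.7%; (8.74 − 2.53)/18 = 34.5% (34.49% before rounding).
4. *Last conception with a term birth by month 18.* 18 − 8.05 = 9.95; 18 − 8.74 = 9.26. A later change could still reach a first trimester until about 9.26 + 2.53 = 11.8 to 9.95 + 2.53 = 12.5 months. Births at 34 and 28 weeks could be conceived up to about months 10.6 and 12.0, so the limit of month 9.3–10 applies to term births only.
5. *Pre-conception exposure.* No observed term birth has more than 9.3–10 months of it, against the 12 months of trying that the article assumes. The mean among post-launch conceptions is 9.26/2 = 4.6 to 9.95/2 = 5.0 months.
6. *Size at which a true effect appears.*

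| Who benefits | Fraction of the effect seen |
|---|---|
| Post-launch conceptions only | 0.515–0.553 |
| Also, fully, pregnancies in the first trimester at launch | 1 − 0.345 = 0.655 to 1 − 0.307 = 0.693 |
| Also later pregnancies, to some degree | above 0.655–0.693, towards 1 |

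As an illustration, take an assumed 10-point fall in caesareans from the 50% in the Background. It would show as 5.1–5.5 points in the first row and 6.6–6.9 in the second.

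7. *Post-launch stratum that is complete by month 18.* A birth at 41 weeks comes 39 × 7/30.44 = 8.97 months after conception, and 9 + 8.97 = 17.97. Conceptions from launch to month 9 are therefore complete up to 41 weeks. They are about 9/18 = half of the births, so intervals widen by √2 ≈ 1.4.

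**The case against.** The strongest reply is that the sentence governs data collection, and that a fuller protocol or analysis plan could still restrict or stratify by conception date. Collecting every birth is indeed right, and the fix needs it. But the sentence also states the comparison for which the births are collected, and nothing in the article qualifies that. Followed as written, it counts pre-launch conceptions as exposed.

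Several other points stand and limit the conclusion.

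- **Half the effect is the worst case.** A reader might infer that the comparison necessarily loses about half of any effect. That needs zero benefit in every pregnancy under way at launch. The article does not say that caesarean section, macrosomia or neonatal admission depend only on early exposure, and its care pathway links to maternity services.
- **A restricted cohort is not clearly more efficient.** Halving the births gains signal relative to noise only while the all-births fraction is below √0.5 = 0.707. The gain is √0.5/0.553 = 1.28 to √0.5/0.515 = 1.37 in the worst case, but only √0.5/0.693 = 1.02 to √0.5/0.655 = 1.08 with full first-trimester benefit. It vanishes if pre-launch conceptions receive (0.707 − 0.553)/0.447 ≈ 35% to (0.707 − 0.515)/0.485 ≈ 40% of the effect. The documents therefore do not support replacing the all-births comparison.
- **Case counts are not fixed.** It is tempting to turn the shares into numbers of births. The sample size section expects 120–150 pregnancies in the boroughs, "with 40–50 pregnancies in the women attending the PREPARED exposed practices", whereas the Abstract ties 80–100 to the women in the 30 practices. The shares do not depend on this choice; counts would.
- **Steering of the programme is not shown to be affected.** Outcome data do enter the charts ("then monthly to generate run charts monitoring process and outcome performance"), and one might infer that early birth data would misguide refinements. The Study design section bases boosting on pre-pregnancy care metrics, so the article does not support that.
- **Birth outcomes are not the headline.** The performance target concerns preparation markers.

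**Conclusion.** The concern holds for the birth-outcome comparison only. Under even conceptions and term birth at 37–40 weeks, about 45–49% of in-window term births were conceived before launch, including the 31–34% already past the first trimester, and none was conceived after about month 9.3–10. The misclassification biases the exposed–unexposed difference towards zero. The effect seen is 51–55% of the true one if pregnancies under way gain nothing, 66–69% if those in the first trimester gain fully, and nearer full size if later pregnancies gain too. The documents cannot say which applies.

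The 30% target is essentially unaffected: it concerns preparation markers at the final observation, and booking measures are recorded early in pregnancy, with a much shorter lag than births. The point deserves a change because it alters what the birth comparison can conclude, and it can be corrected from routinely collected data.

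**What to change.** - **Derive conception month.** Use birth date minus gestation in weeks. The hospital extract already covers gestation in some form ("The birth outcome data includes: term and status of infant at birth"); if it is held only as term or preterm, add weeks. Because "All data will be anonymised at source by hospital/practice administrators", hospital administrators should derive the month before release.
- **Split the comparison.** Report birth outcomes in exposed and unexposed practices alike, by conception before or after launch, and keep the all-births comparison alongside.
- **Tie claims to the right stratum.** Base any statement about the effect of pre-pregnancy exposure on conceptions from launch to about month 9. Report later conceptions only descriptively, since they enter the window only as losses or preterm births.
- **State the limit.** Say that birth outcomes reflect the programme as delivered up to about month 9–10, not the final optimised version.

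The cost is one derived field and some wording. The downside is about half as many births in the post-launch stratum, intervals about 1.4 times wider, and a narrower claim. The split does not give any woman the full 12 months of exposure before conception. Longer birth follow-up is a separate decision and not part of this change.
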